### Health education group (HE)

In the HE, participants receive a folder via WhatsApp or e-mail with information related to breast cancer management once a week. In addition, 2 days after, the ABRACE team and a small group of participants (i.e., maximum of three patients) discuss the target topic of the week in an online session, via videoconference, lasting approximately 30 min. The first session of the health education program will be delivered individually (i.e., 1:1 supervision ratio) to provide a more comfortable environment for the participant to express cancer-related barriers and concerns. The topics approached in the 12 weeks are the following: anxiety and depressive symptoms, fatigue, body image, body composition and bone health, symptoms in the arm and breast, vasomotor symptoms, peripheral neuropathy, pain and arthralgia, sexual dysfunction, quality of life, physical activity, and eating habits. Also, the conversations aim to encourage the participants to increase their physical activity levels following the current guidelines of 150 min per week of moderate aerobic exercise [9]. The MTHE will receive the same folder.

#### Criteria for discontinuing allocated interventions

Participants may be discontinued from the study for safety reasons or withdrawal of participant’s consent. For participants allocated to any group, medical advice, disease complication, or a severe health event during the study, which precludes attendance to intervention sessions, are considered criteria for interrupting participation in the study. Even participants who have discontinued the interventions will continue to be contacted by the study and invited for final evaluations.

#### Strategies for trial retention

Participants allocated to both groups will receive text messages to reinforce the date and time of interventions 2 days before each session. We will use phone calls or WhatsApp messages to ask participants about their reasons for not attending the session. There are no prohibited concomitant interventions; however, any systematic or supervised physical exercise should be reported by the participants and documented for future discussions.

#### Outcomes

Standardized methodological procedures for outcomes assessment are listed below.

### Primary outcome

The primary study outcome is cancer-related fatigue, which will be assessed using the Piper fatigue scale. Cancer-related fatigue was chosen as the primary outcome because it is a widespread side effect caused by chemotherapy, and it is identified among high-priority cancer- and treatment-related toxicities based on its potential to affect cancer care rapidly [28, 38].

### Secondary outcomes

Additional outcomes that are clinically relevant for breast cancer patients will be assessed by online questionnaires, including quality of life, symptoms of depression and anxiety, physical activity level, and cancer-related cognitive function. In addition, a functional performance test will be held by video call. These outcomes are evaluated before and after 12 weeks of intervention.

### Other outcomes

Other outcomes include sociodemographic, clinic characteristics, and self-reported anthropometric measures assessed at baseline. After 12 weeks of intervention, a follow-up questionnaire evaluating the individual motivation perception, lifestyle changes, and main barriers to group participation will be carried out. Also, adherence to interventions will be reported as group attendance and compliance with protocol sessions.

### Safety outcomes

A medical clearance for physical exercise provided by their oncologist is requested for each patient. We will collect and manage spontaneously reported adverse events. Such events will be classified according to their severity (i.e., mild, moderate, severe), predictability (i.e., expected or unexpected), and potential relation with study procedures (i.e., definitely related, possibly related, or unrelated) [37]. All cases of adverse events will be discussed and, if necessary, adjudicated by at least two out of the following investigators: principal investigator ([name]), study manager ([name]), and medical and expert consultants.

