### Multicomponent training and health education group (MTHE)

The MTHE will be performed twice a week over 12 weeks, on pre-established and non-consecutive days. The sessions will be held by video call on Google Meet platform (approximately 60 min of duration) in small groups (maximum of three patients) and are supervised by physical education students or professionals previously trained to carry out the intervention. The first session of the training program will be performed individually (i.e., 1:1 supervision ratio) to ensure adequate orientation. All equipment and materials will be delivered to participants at the beginning of the intervention (i.e., two pairs of 2- and 4-kg dumbbells and one exercise mattress). The exercises within a training session will be ordered as follows: warm-up (joint mobilization and aerobic stimulus), balance exercise, resistance exercise, and stretching of the main muscles used during the training session. The training periodization used throughout the 12 weeks can be seen in Table 1.

**Table 1 Tab1:** Training periodization and exercises used throughout the 12 weeks intervention in the MTHE group

Volume	Weeks 1–4	Weeks 5–8	Weeks 9–12
Joint mobilization: 2 sets × 10 repetitions each	Joint mobilization: Stiff and shoulder front raise	Joint mobilization: Stiff and shoulder front raise	Joint mobilization: Stiff and shoulder front raise
Aerobic stimulus: 2–3 sets × 20 s	Aerobic (2 sets): Skipping	Aerobic (2 sets): Adapted Jumping jacks	Aerobic (3 sets): Skipping (session A); Jumping jacks (session B)
Balance exercises: 2 sets × 20 s	Balance: Single leg stance (Right leg + Left leg)	Balance: Imaginary line walking	Balance: Airplane Pose (Right leg + Left leg)
Resistance exercises: 2–3 sets × 10–15 repetitions 10 exercises	Resistance (2 sets × 10–12 repetitions, 5–6 OMNI) exercises (a):	Resistance (2–3* sets × 10–12 repetitions, 6–7 OMNI) exercises (b):	Resistance (2–3* sets × 12–15 repetitions, 7–8 OMNI) exercises:

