The cool-down phase will last 5–10 min, during which participants will perform static stretching exercises on major muscle groups (pectoralis major, latissimus dorsi, hamstring, adductor, and glutes) for one set of 20 s each. Additionally, in the second training session of each week, after stretching exercises, the supervisor will address one health education topic, based on the same contents planned for the health education group, but more briefly, lasting 15–20 min. All participants will be instructed to report difficulties and limitations, and training variables (i.e., RPE, load, cadence, and total volume) or any exercise adaptation are registered.

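### Adverse events are collected by spontaneous report while MTHE has twice the live sessions of HE, so counts by arm may be biased by unequal opportunity to report

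*Protocol article*

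**What the plan says.** The Safety outcomes section fixes the method of collection: "We will collect and manage spontaneously reported adverse events". Events are then classified by severity, predictability and relation to study procedures, and adjudicated where necessary. The section on harms defines a serious event but adds no method of eliciting events. Table 2 lists no adverse-event item at any time point.

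The contact schedules differ by arm:

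- **MTHE:** "The MTHE will be performed twice a week over 12 weeks", in live sessions of about 60 minutes. In the second session of each week the supervisor adds an education topic, "based on the same contents planned for the health education group, but more briefly, lasting 15–20 min".
- **HE:** "participants receive a folder via WhatsApp or e-mail with information related to breast cancer management once a week". Two days later the women and the team "discuss the target topic of the week in an online session, via videoconference, lasting approximately 30 min".

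The MTHE section also states "All participants will be instructed to report difficulties and limitations", in a sentence that goes on to the recording of training variables and exercise adaptations. MTHE women are asked about exertion after each exercise. The HE section has no counterpart to either.

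Statistical considerations says that categorical variables will be summarised by intervention group. It names no between-arm test of adverse events.

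**The concern.** Under spontaneous reporting, an event is recorded when a woman happens to mention it to staff. If one arm meets staff twice as often, its events have more chances to be mentioned even when the true rates are equal. The women are on or shortly after chemotherapy, so there is background illness to report in both arms.

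At stake is the reading of the safety summary. Supervised exercise could look less safe than education alone because it was observed more closely. With about 15 women per arm and no data monitoring committee, a few unrecorded events in HE would change the picture. Events that nobody volunteers can also be lost in MTHE.

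**Working it through.** The plan gives no adverse-event rate or reporting probability, so there is no figure of its own to reproduce. The check is of contact counts first, then of what they could do to recorded counts.

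**1. Scheduled live sessions** (MTHE and HE sections)

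- MTHE: 2 per week × 12 weeks = 24
- HE: 1 per week × 12 weeks = 12
- Ratio 24/12 = 2.0. The per-protocol cut-offs of 16 and 8 sessions stand in the same 2:1 ratio.

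**2. Contact time**

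- MTHE at the stated length: 24 × 60 = 1,440 min. HE: 12 × 30 = 360 min. Ratio 4.0.
- If the 15–20 min of education comes on top of the 60 min: 1,440 + 12 × 15 = 1,620, or 1,440 + 12 × 20 = 1,680 min. Ratio 4.5 to 4.7.

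Much of the MTHE time is exercise rather than talk, so the number of sessions is the safer measure of opportunity.

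**3. Effect on recorded events when the true rates are equal**

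Assume that an event stays reportable for *w* weeks and that each contact reveals it with probability *q*, the same in both arms and independent between contacts. Neither value is in the article.

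- Detection in MTHE: 1 − (1 − q)^(2w)
- Detection in HE: 1 − (1 − q)^w
- Ratio: 1 + (1 − q)^w, which lies between 1 and 2 whatever the true event rate

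| Reportable for | q = 0.1 | q = 0.3 | q = 0.5 | q = 0.9 |
|---|---|---|---|---|
| 1 week | 0.19 / 0.10 = 1.90 | 0.51 / 0.30 = 1.70 | 0.75 / 0.50 = 1.50 | 0.99 / 0.90 = 1.10 |
| 2 weeks | 0.344 / 0.19 = 1.81 | 0.76 / 0.51 = 1.49 | 0.938 / 0.75 = 1.25 | 1.00 / 0.99 = 1.01 |
| 4 weeks | 0.570 / 0.344 = 1.66 | 0.942 / 0.76 = 1.24 | 0.996 / 0.938 = 1.06 | 1.00 / 1.00 = 1.00 |

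**4. In women**

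Take 15 per arm, a true event proportion of 50% (assumed), q = 0.5 and w = 1. MTHE records 15 × 0.5 × 0.75 = 5.6 women and HE records 15 × 0.5 × 0.5 = 3.8. The gap of about two women comes from ascertainment alone.

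**5. Sensitivity to equal q**

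If HE women were twice as likely to mention an event at a contact (q = 0.2 against 0.1, w = 1), the detection probabilities would be 0.19 in MTHE and 0.20 in HE, a ratio of 0.95. The direction therefore depends on the reporting probability being similar in the two arms.

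If both arms are asked the same question on the same schedule, the ratio in this model is 1.0 by construction.

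**The case against.** The strongest reply is that spontaneous reporting is a disclosed choice in a small trial with limited resources, that no formal harm comparison is stated, and that events have other routes into the record in both arms. Non-attenders are asked why. Women who discontinue are still contacted and invited to final evaluations. Withdrawal reasons are documented case by case. The follow-up questionnaire covers safety, and the QLQ-C30 and QLQ-BR23 ask about symptoms identically in both arms. HE sessions are also live discussions of topics such as fatigue, pain and arm symptoms, and cover them at greater length than MTHE does.

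Part of this stands. There is no between-arm test to invalidate, and the HE discussions may raise the chance of a mention per contact, as step 5 allows. But the other routes do not record events equally in both arms as they occur. Calls about missed sessions are triggered per session and reach only absentees. Withdrawal notes cover only those who leave. The follow-up questionnaire records agreement on a 7-point scale, and the QLQ scales give scores at two time points.

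A reader might go further and infer that HE events are missed, that the arms cannot be compared, or that the bias can be quantified. One could compute, for example, that with a 5% chance of a mention at each contact, 1 − 0.95^24 = 71% of MTHE women and 1 − 0.95^12 = 46% of HE women would have a report. The documents do not support these readings. They give no reporting probability, that formula contains no event rate, and lasting or readily volunteered events would be recorded almost equally. The instruction to report difficulties is also worded for all participants and concerns training, so it is weak evidence of unequal prompting.

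**Conclusion.** The concern holds as a risk of bias in the descriptive safety summary. Collection is unsolicited by the article's own statement, scheduled contacts are exactly 2:1, and Table 2 has no common adverse-event question to offset this. Mild and moderate events are likely to be under-recorded in HE. Serious events that need hospitalisation would probably surface in either arm.

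The apparent MTHE:HE ratio with equal true rates could be anywhere from about 1.0 to about 1.9 over the values examined. That range rests on an assumed reporting probability, equal in the two arms and independent between contacts, and on an assumed period during which an event is reportable. The primary outcome and its analysis are not affected. The point is worth acting on because a better method costs very little.

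**What to change.** - **Weekly question.** Ask one identical open adverse-event question once a week in both arms, at the education contact that both already have (the second weekly session in MTHE, the weekly discussion in HE). The unblinded session staff record the answer. When that contact is missed, put the same question in the existing call or message to the absentee.
- **End of trial.** Ask it once more through unblinded staff, for example on final evaluation day 1, where the researcher monitoring the physical activity and cognitive questionnaires is already unblinded. It should not be asked by the blinded assessor who conducts the fatigue interview, because the answer could reveal the allocation.
- **Reporting.** Summarise solicited events by arm. List spontaneous reports and events during exercise separately, so that no safety information is lost.
- **Women enrolled before the change.** Report their events separately and label them as spontaneous-only. Recruitment was planned to end in March 2023 and the article appeared in January 2023, so this may be a large share. For them, state the number of contacts per arm beside the counts.

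The cost is about a minute per weekly contact and one form field, with no extra staff. Recorded counts will rise in both arms, and a mid-trial change leaves two ascertainment periods that should not be pooled.

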#### Sample size

The sample size estimation was based on the number of patients feasible to collect given our financial resources during the period of the study (concomitant with the COVID-19 pandemic )[29]. We estimate that the total sample will be around 30 participants. Therefore, approximately 15 women will be enrolled in each group.

#### Assignment of interventions and blinding

After consent, each participant will receive an internal identifier number. After completing the baseline assessments, participants are randomized to either the MTHE or HE. A blinded investigator created a computer-generated randomization sequence, via random function (Excel software), 1:1 ratio, with a block of random sizes that are not disclosed to ensure concealment. The allocation concealment is implemented by researchers in charge of requesting randomization for one of the blind investigators with access to the randomization list ([name], [name]), via email, from the identifier number. A researcher ([name]) allocates individuals in the groups by phone call or WhatsApp message. Randomization requests follow the order in which participants complete the baseline assessments. The allocation date of the participants is recorded in an Excel spreadsheet.

Blinding will be applied for assessors of all primary and secondary outcomes, except physical activity level and cognitive function (the researcher monitoring these two evaluations is not blinded, but both questionnaires are self-administered). Participants are asked to omit their assigned group and not talk about their interventions during the outcome assessments. Due to the nature of the intervention, the study staff supervising training sessions and participants are non-blinding. In unblinding cases, the principal investigator will be notified with the participant ID, date, and reasons for unblinding.

#### Data collection

On the first day, previous physical activity levels and cognitive function will be assessed. After at least a 48-h interval from the first day, primary and all other secondary outcomes will be measured. During the assessments a video call (Google Meet) will be held with each participant individually. The evaluators were trained before starting the trial, and periodic meetings and written communication between the evaluators will be established fortnightly to promote internal transparency and consolidate data collection procedures. The time scheme for study conduction is presented in Table 2.

**Table 2 Tab2:** Time scheme for ABRACE: Telehealth conduction

Study period							
	Enrolment and baseline measures	Baseline measures	Allocation	Post-allocation		Close out	
**Timepoint**	**t**_**0**_	**t**_***1***_	***t***_***2***_	***t***_***3***_	***t***_***4***_	***t***_***5***_	***t***_***6***_
Timepoint description	Interview and baseline evaluations day 1	Baseline evaluation day 2	-	Intervention start	Intervention end	Final evaluation day 1	Final evaluation day 2
**Enrolment**							
Eligibility screening	x						
Informed consent	x						
Allocation			x				
**Interventions**							
Multicomponent Training Group plus Health Education				x	x		
Health Education Group				x	x		
**Assessments**							
Primary outcomes							
Cancer-related fatigue		x					x
Secondary outcomes							
Quality of life		x					x
Depression symptoms		x					x
Anxiety symptoms		x					x
Functional test		x					x
Cognitive function	x					x	
Physical activity level	x					x	

#### Assessment of primary outcome

##### Cancer-related fatigue

Cancer-related fatigue is determined through an interview by scores from the Piper Fatigue Scale, the Portuguese-validated version [35, 41]. Piper Fatigue Scale consists of 22 items, ranging from 0 (no fatigue) to 10 (severe fatigue), to assess four dimensions of subjective fatigue and total fatigue. Six items will evaluate behavioral fatigue (i.e., impact of fatigue on school or work, interacting with friends, and the overall interference with enjoyable activities). The affective fatigue includes five items that assess the emotional meaning attributed to fatigue. Other five items comprise the sensory fatigue (i.e., mental, physical, and emotional fatigue symptoms). The cognitive/mood fatigue includes six items to assess the impact of fatigue on concentration, memory, and the ability to think clearly. Total fatigue is measured by averaging these four dimensions.

#### Assessments of secondary outcomes

##### Quality of life

The Brazilian version of the self-report 30-item EORTC QLQ-C30 (version 3.0) will be used to assess the quality of life [1, 33]. Scores will be derived and scaled from 0 to 100 according to the EORTC scoring manual [16], considering the global health status scale and five multi-item functional scales (i.e., physical, emotional, role, cognitive, and social function), with higher scores indicating better quality of life, and also, three multi-item and six single-item symptom scales, with higher scores representing higher levels of complications. In addition, the supplementary 23-item breast cancer-specific module (EORTC QLQ-BR23) is also applied and scored as well. The QLQ-BR23 incorporates five multi-item scales to assess body image, sexual functioning, systemic therapy side effects, breast symptoms, and arm symptoms. In addition, single items will assess sexual enjoyment, future perspective, and hair loss. The scoring approach for this questionnaire is identical in principle to that for the function and symptom scales of the QLQ-C30, where a higher score for the functional scales represents a healthier level of functioning, while a higher score for the symptom scales represents a higher level of symptomatology.

##### Depressive symptoms

Depressive symptoms will be assessed by the Center for Epidemiological Studies – Depression (CES-D) scale, the Portuguese-validated version [19, 42]. This self-report questionnaire, previously used in oncology patients [32], comprises 20 items to assess the individual’s current state, asking about the frequency of symptoms in the last 7 days. Each answer is scored according to an order of frequency of symptoms ranging from 0 (rarely or never) to 3 scores (always). The total score ranged from 0 to 60, with higher values indicating a higher level of depression.

##### Anxiety symptoms

Anxiety symptoms are assessed by the State-Trait Anxiety Inventory, a self-report instrument [49]. The questionnaire comprises two parallel scales to evaluate the trait anxiety and state anxiety, each one with 20 items. The scores for individual items ranged from 1 (“almost never”) to 4 (“almost always”), with a total score ranging from 20 to 80 for each scale.

##### Physical activity level

Self-reported physical activity level is assessed using a translated and validated Brazilian version of Godin-Shepard questionnaire [18, 46]. Participants should report the number of times per week that they engage in vigorous, moderate, and light physical activity over a period greater than 15 min. The frequency is multiplied by a specific coefficient for each intensity, which corresponds to the metabolic equivalent of the task (MET). High scores indicate a higher level of physical activity during free time.

#### Cancer-related cognitive function

The FACT-Cognitive Function [56] is a self-reported questionnaire used to assess cognitive complaints in cancer patients. It consists of four blocks of questions that must be interpreted by assigning answers from 0 (“never”) to 4 (“several times a day”) for the last 7 days. The score is presented in subscales referring to perceived cognitive deficits, comments from other people, perceived cognitive skills, and quality of life impact. Higher scores represent a better cognitive function.

##### Functional capacity

The lower limb functional performance is assessed through the sit-to-stand test [43]. The participant starts seated in the chair, with her back supported and her feet shoulder-width apart and fully supported on the floor. The upper limbs will be crossed against the chest. After two test attempts, at the evaluator’s “start” signal, the participants get up and sit down as many times as possible for 30 s, with correct execution. The intra-rater reliability for this test is reported as 0.88 in a previous study [58] evaluating sit and stand test remotely by video in older adults with cancer.

#### Other outcomes

##### Sociodemographic and clinical characteristics

A questionnaire will be applied to assess health parameters and characterize the sample. Sociodemographic factors and data on histological type of tumor, stage, the status of hormone receptors, expression of HER-2 and chemotherapy, immunotherapy, or radiation therapy protocols used will be collected and/or confirmed directly with the responsible doctor, with prior authorization from each patient.

